## Abstract

**Background:**

Evidence concerning the importance of glucose lowering in the prevention of cardiovascular (CV) outcomes remains controversial. Given the multi-faceted pathogenesis of atherosclerosis in diabetes, it is likely that any intervention to mitigate this risk must address CV risk factors beyond glycemia alone. The SGLT-2 inhibitor empagliflozin improves glucose control, body weight and blood pressure when used as monotherapy or add-on to other antihyperglycemic agents in patients with type 2 diabetes. The aim of the ongoing EMPA-REG OUTCOME™ trial is to determine the long-term CV safety of empagliflozin, as well as investigating potential benefits on macro-/microvascular outcomes.

**Methods:**

Patients who were drug-naïve (HbA_1c_ ≥7.0% and ≤9.0%), or on background glucose-lowering therapy (HbA_1c_ ≥7.0% and ≤10.0%), and were at high risk of CV events, were randomized (1:1:1) and treated with empagliflozin 10 mg, empagliflozin 25 mg, or placebo (double blind, double dummy) superimposed upon the standard of care. The primary outcome is time to first occurrence of CV death, non-fatal myocardial infarction, or non-fatal stroke. CV events will be prospectively adjudicated by an independent Clinical Events Committee. The trial will continue until ≥691 confirmed primary outcome events have occurred, providing a power of 90% to yield an upper limit of the adjusted 95% CI for a hazard ratio of <1.3 with a one-sided α of 0.025, assuming equal risks between placebo and empagliflozin (both doses pooled). Hierarchical testing for superiority will follow for the primary outcome and key secondary outcomes (time to first occurrence of CV death, non-fatal myocardial infarction, non-fatal stroke or hospitalization for unstable angina pectoris) where non-inferiority is achieved.

**Results:**

Between Sept 2010 and April 2013, 592 clinical sites randomized and treated 7034 patients (41% from Europe, 20% from North America, and 19% from Asia). At baseline, the mean age was 63 ± 9 years, BMI 30.6 ± 5.3 kg/m^2^, HbA1c 8.1 ± 0.8%, and eGFR 74 ± 21 ml/min/1.73 m^2^. The study is expected to report in 2015.

**Discussion:**

EMPA-REG OUTCOME™ will determine the CV safety of empagliflozin in a cohort of patients with type 2 diabetes and high CV risk, with the potential to show cardioprotection.

**Trial registration:**

Clinicaltrials.gov NCT01131676

## Introduction

Type 2 diabetes mellitus (T2DM) is frequently associated with comorbidities that exacerbate cardiovascular (CV) risk, such as obesity and hypertension [1]. The risk of CV disease is increased approximately two to four-fold in adults with diabetes even after adjustment for conventional risk factors (age, sex, smoking status, body mass index [BMI], systolic blood pressure [BP], and lipids) [2]. Recommended strategies for reducing CV risk in patients with T2DM include glucose management, lipid lowering, BP control, smoking cessation, and weight loss [1]. Improved glycemic control has been associated with a reduction in microvascular events [3] and there is a clear association between microvascular complications such as albuminuria and an increased risk of CV events in patients with T2DM [4]. However, the impact of reducing blood glucose, and the potential benefit of specific glucose-lowering agents, on CV events in patients with T2DM remains unclear and highly controversial [5,6]. Moreover, treatment must likely occur over a substantial duration of time, since macrovascular outcome events are known to be late complications of a progressive multifaceted pathogenic process that spans decades [7,8]. Lately, regulatory authorities have issued guidance for evaluating the long-term CV safety of new anti-diabetes agents to ensure that CV safety is demonstrated with reasonable assurance [9,10]. These mandated trials provide an opportunity to potentially demonstrate CV as well as microvascular benefits of new anti-diabetes drugs.

Sodium glucose cotransporter 2 (SGLT2) inhibitors are a new class of antidiabetes agents that reduce hyperglycemia in patients with T2DM by reducing renal glucose reabsorption and thus increasing urinary glucose excretion (UGE) [11]. Empagliflozin is a potent and selective inhibitor of SGLT2 [12]. In placebo-controlled phase III trials in patients with T2DM, empagliflozin used as monotherapy or add-on therapy improved hemoglobin A1c (HbA1c) approximately 0.7-1.0% -point (depending on baseline HbA1c and renal function) with a low risk of hypoglycemia, reduced body weight and BP, without increases in heart rate, and had small effects on plasma lipids (increase in HDL-cholesterol, increase in LDL-cholesterol, no change in LDL/HDL cholesterol ratio) [13-17]. In addition, empagliflozin has been shown to improve arterial stiffness and reduce glomerular hyperfiltration in patients with type 1 diabetes mellitus (T1DM) [18,19]. Moreover, SGLT2 inhibitors have also been reported to reduce other CV risk markers such as visceral fat mass [20,21] and proteinuria [22]. Based on these pleiotropic effects on CV risk factors, we hypothesized that empagliflozin may reduce CV risk in patients with T2DM.

The EMPA-REG OUTCOME™ trial was designed to determine the long-term CV safety of empagliflozin in patients with T2DM and to investigate its potential cardioprotective effects, as well as impact on microvascular outcomes, in a dedicated study that complied with current regulatory requirements.

## Methods

The EMPA-REG OUTCOME™ trial (clinicaltrials.gov identifier: NCT01131676) is an ongoing, multicenter, randomized, double-blind, placebo-controlled trial. It was designed to assess the effect of empagliflozin (10 mg or 25 mg once daily) compared with placebo, in addition to standard of care, on CV events in adults with T2DM at high risk of CV events and with less than optimized glycemic control.

The study protocol was approved by the respective Institutional Review Boards, Independent Ethics Committees and Competent Authorities according to national and international regulations.

### Trial population

Our goal was to recruit 7000 participants across 42 countries. Patients aged ≥18 years (≥20 years in Japan and also ≤65 years in India) with T2DM who were drug-naïve (no anti-diabetes agents for ≥12 weeks prior to randomization) with HbA1c ≥7.0% and ≤9.0% or taking any background anti-diabetes therapy (except pioglitazone in Japan) with HbA1c ≥7.0% and ≤10.0% despite diet and exercise counseling and who were at high risk of CV events were eligible for inclusion. The main inclusion criteria are provided in detail in Table 1. The dose of background glucose-lowering therapy was required to be unchanged for ≥12 weeks prior to randomization or, in the case of insulin, unchanged by >10% from the dose at randomization in the previous 12 weeks. Subjects were required to have a BMI ≤45 kg/m^2^ at baseline. Detailed inclusion and exclusion criteria are listed in Additional file 1.

**Table 1 T1:** Key inclusion criteria

**Insufficient glycemic control**	**High risk of cardiovascular events (≥1 of the following)**
• ** *Drug-naive subjects* ****:** HbA_1c_ ≥7.0% and ≤9.0% at screening	• History of myocardial infarction >2 months prior to informed consent
	• Evidence of multi-vessel CAD i.e. in ≥ 2 major coronary arteries or the left main coronary artery, documented by any of the following:
• ** *Subjects on background therapy* ****:** HbA_1c_ ≥7.0% and ≤10.0% at screening	– Presence of significant stenosis: ≥50% luminal narrowing during angiography (coronary or multi-slice computed tomography)
	– Previous revascularization (percutaneous transluminal coronary angioplasty ± stent or coronary artery bypass graft >2 months prior to consent
	– The combination of revascularization in one major coronary artery and significant stenosis (≥50% luminal narrowing) in another major coronary artery
	• Evidence of single-vessel CAD, ≥50% luminal narrowing during angiography (coronary or multi-slice computed tomography) not subsequently successfully revascularized, with at least 1 of the following:
	– A positive non-invasive stress test for ischemia
	– Hospital discharge for unstable angina ≤12 months prior to consent
	• Unstable angina >2 months prior to consent with evidence of single- or multi-vessel CAD
	• History of stroke (ischemic or hemorrhagic) >2 months prior to consent
	• Occlusive peripheral artery disease documented by any of the following:
	– Limb angioplasty, stenting, or bypass surgery
	– Limb or foot amputation due to circulatory insufficiency
	– Evidence of significant peripheral artery stenosis (>50% on angiography, or >50% or hemodynamically significant via non-invasive methods ) in 1 limb
	– Ankle brachial index <0.9 in ≥1 ankle

CAD, coronary artery disease.

### Study design

Eligible patients underwent a 2-week, open-label, placebo run-in period (Figure 1) during which background glucose-lowering therapy was continued unchanged. The purpose of the run-in period was to evaluate participants’ willingness to adhere to the long-term treatment and follow-up planned in the trial. Following the placebo run-in, patients still meeting the inclusion/exclusion criteria were randomized (1:1:1) to receive empagliflozin 10 mg, empagliflozin 25 mg, or placebo once daily in addition to their background therapy. Background glucose-lowering therapy was to remain unchanged for the first 12 weeks after randomization if possible, although rescue therapy could be initiated (details in Additional file 2). After this period, therapy could be adjusted to achieve desired glycemic control at the investigator’s discretion to achieve best standard of care according to local guidelines. Investigators were encouraged to treat all other CV risk factors according to local standard of care.

**Figure 1 F1:**
[figure not shown]
Study design.

### Randomization and follow-up

Randomization was undertaken using a computer-generated random sequence and an interactive voice and web response system. Patients were stratified by HbA_1c_ at screening (<8.5%, ≥8.5%), BMI at randomization (<30 kg/m^2^, ≥30 kg/m^2^), region (North America [plus Australia and New Zealand], Latin America, Europe, Africa, Asia), and renal function (eGFR using the Modification of Diet in Renal Disease [MDRD] equation) at screening (Chronic Kidney Disease [CKD] stage 1: ≥90 ml/min/1.73 m^2^; CKD stage 2: 60–89 ml/min/1.73 m^2^; CKD stage 3: 30–59 ml/min/1.73 m^2^). Patients are instructed to attend the clinic at pre-specified times over the duration of the study including a follow-up visit 30 days after the end of the treatment period (Figure 1). Patients who prematurely discontinue study medication are asked to attend all visits as originally planned.

### Outcomes and outcome adjudication

The primary outcome of the study is time to first occurrence of CV death, non-fatal myocardial infarction (MI, excluding silent MI), or non-fatal stroke *i.e.,* 3-point major adverse cardiovascular events (3P-MACE). The key secondary outcome expands the primary composite outcome to include time to first occurrence of hospitalization for unstable angina (4P-MACE). Further CV outcomes are the individual components of the 4P-MACE, as well as individual occurrence of and time to silent MI, heart failure requiring hospitalization, all-cause mortality, transient ischemic attack (TIA) and coronary revascularization procedures. All CV outcome events and deaths are being prospectively adjudicated by the Clinical Events Committee (one for cardiac events and one for neurological events), as recommended in FDA guidelines (FDA [9]). Definitions of the major clinical outcomes are presented in Additional file 3 and a non-exhaustive list of further CV outcomes (secondary, tertiary and exploratory) in Additional file 4.

Additional secondary outcomes include the occurrence of and time to new onset albuminuria (urinary albumin:creatinine ratio ≥30 mg/g) and new onset of macroalbuminuria (urinary albumin:creatinine ratio ≥300 mg/g). Other outcomes include the occurrence of and time to a composite microvascular outcome comprising the initiation of laser therapy for retinopathy, vitreous hemorrhage, diabetes-related blindness, and new or worsening nephropathy (new onset macroalbuminuria [albumin:creatinine ratio ≥300 mg/g]; doubling of serum creatinine accompanied by eGFR ≤45 mL/min/1.73 m^2^; initiation of renal replacement therapy; or death due to renal disease) as well as the individual components of this composite.

The short (12 weeks), medium (52 weeks), and long-term (annually, at end of study, and at follow-up) effects of the two doses of empagliflozin on HbA_1c_, fasting plasma glucose (FPG), body weight, waist circumference, and BP will be assessed, as well as the proportion of patients who meet the composite outcome of HbA_1c_ reduction ≥0.5%, systolic BP reduction >3 mmHg, and body weight reduction >2%.

The prognostic impact of, and the modulating potential of empagliflozin on, the renal biomarker cystatin C and the CV biomarkers high-sensitivity C-reactive protein and high sensitivity troponin T will be assessed in sub-studies, as will potential associations between genetic variations and drug response.

Safety will be assessed based on adverse events (AEs) reported throughout the study and up to 7 days after the last dose of study medication (coded using the Medical Dictionary for Drug Regulatory Activities [MedDRA]), clinical laboratory tests, vital signs, 12-lead electrocardiogram (ECG), physical examination, and the use of rescue medication. Pre-specified AEs of special interest (AESI) include confirmed hypoglycemic adverse events (plasma glucose ≤70 mg/dL (3.9 mmol/L) and/or requiring assistance), those reflecting volume depletion, bone fracture, hepatic events, malignancies, urinary tract infection (UTI), and genital infection. Events may be defined by either abnormal laboratory values and/or relevant adverse events identified using prospectively defined search categories or both. For qualifying events, relevant source documentation will be requested including lab values, histological analysis, results of ultrasound, CT, MRI, scintigraphy, hospital discharge letters, and medical reports from other physicians. All evaluations will be performed in a blinded fashion.

A list of efficacy and safety outcomes is presented in Additional file 4.

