#### Analysis plan

Three analysis populations are defined for this trial: 1) The treated set (TS), consisting of all patients who were treated with at least one dose of study drug, 2) The on-treatment set (OS), consisting of patients who received the drug for at least 30 days (cumulative) in whom events will be considered that occurred within 30 days of the off-treatment period or until the end of the entire trial, whichever will be earlier (patients who did not experience the primary outcome will be censored at the end of the treatment period, if the patient completes treatment as planned, or at the end of the 30 day period) and 3) the Full Analysis Set (FAS), consisting of all patients randomized, treated with at least one dose of study drug and with a baseline HbA1c value.

The primary analysis will be based on a Cox proportional hazards model with treatment (with empagliflozin 10 mg and 25 mg pooled into a single group), age, gender, baseline BMI (<30 kg/m^2^, ≥30 kg/m^2^), baseline HbA_1c_ (<8.5%, ≥8.5%), baseline eGFR as well as geographical region (classified as North America, Latin America, Europe, Africa and Asia) as factors. The same Cox proportional hazards model as for the primary outcome will be employed in all steps of the hierarchical testing strategy (3P-MACE and 4P-MACE).

The time to the occurrence of the primary outcome and the key secondary outcomes event will be computed as (event date - randomization date) +1. Patients who do not have the event during the trial period will be censored at the individual day of trial completion. The time to censoring will be computed as (individual day of trial completion – randomization date) + 1. For patients who have more than one primary outcome event during the trial, the time to the first occurrence of the primary outcome event will be considered for the primary analysis. All adjudicated and confirmed events will be used for the primary analysis.

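### The single 7-day post-dose adverse event window makes no exception for malignancy or bone fracture, so on its natural reading later diagnoses in early stoppers fall outside the stated safety assessment

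*Protocol article*

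**What the plan says.** The safety paragraph under Outcomes and outcome adjudication gives one window for adverse events: those "reported throughout the study and up to 7 days after the last dose of study medication". It then lists the pre-specified events of special interest. Besides hypoglycaemia these include "those reflecting volume depletion, bone fracture, hepatic events, malignancies, urinary tract infection (UTI), and genital infection". No event type has a different window.

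Three other places bear on this:

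- Randomization and follow-up: "Patients who prematurely discontinue study medication are asked to attend all visits as originally planned". The same section schedules "a follow-up visit 30 days after the end of the treatment period".
- Analysis plan, for the primary and key secondary outcomes: "Patients who do not have the event during the trial period will be censored at the individual day of trial completion". For the on-treatment set, "events will be considered that occurred within 30 days of the off-treatment period or until the end of the entire trial, whichever will be earlier".
- Outcomes and outcome adjudication: "All CV outcome events and deaths are being prospectively adjudicated by the Clinical Events Committee".

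The article refers to Additional file 4 for the list of safety outcomes. That file is not at hand.

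**The concern.** A window of 7 days after the last dose suits acute, reversible effects such as hypoglycaemia, volume depletion or genital infection. It suits malignancy and fracture less well. A malignancy can show itself first as a symptom that leads the patient to stop study drug, with the diagnosis confirmed weeks later. The safety paragraph itself expects histology and imaging for qualifying events, and such work-up can outlast a week.

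If counting ends 7 days after the last dose, follow-up for these events ends at a point that may be linked to the event itself. If the arms differ in how many patients stop, or in why they stop, the comparison of malignancy and fracture no longer rests on equal follow-up of the randomised groups. A long placebo-controlled trial with 7034 treated patients is a good setting for studying such events, and the plan already intends to keep seeing the patients in whom they would be missed.

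**Working it through.** **Step 1. What the 7-day limit can mean.** The article keeps every group of patients under observation beyond day 7 after the last dose. Completers have a visit 30 days after treatment ends, and early stoppers are asked to attend all planned visits. If adverse events counted over all of that time, the 7-day limit would exclude nothing. It has an effect only as a cut-off tied to dosing. For an early stopper, two readings remain:

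- Natural reading: the cut-off is 7 days after that patient's own last dose.
- Alternative reading: the window covers the planned treatment period, including time off drug, and the 7 days extend it only at the planned end.

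The article does not say which applies.

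**Step 2. Windows side by side.**

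| Outcome | End of counting in the article |
|---|---|
| Primary and key secondary outcomes | Individual trial completion |
| Primary outcome, on-treatment set | 30 days off treatment, or trial end if earlier |
| Adverse events, with malignancy and fracture not exempted | 7 days after last dose |

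The shortest post-dose limit applies to adverse events, and the delayed ones are not exempted.

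**Step 3. Patient-time excluded under the natural reading.** The article gives no figure to reproduce here, so everything below except the 7034 treated patients is assumed. Let *d* be the proportion who stop early over follow-up *T*, with a constant stopping hazard λ = −ln(1 − *d*)/*T*. All patients are taken to remain in follow-up to *T*.

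- Mean time on drug as a share of *T* is *d*/(−ln(1 − *d*)).
- The window of *w* = 7/365.25 years adds back about *d*·*w*/*T*.
- Share excluded ≈ 1 − *d*/(−ln(1 − *d*)) − *d*·*w*/*T*.

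With *T* = 3 years:

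| Stop early | 1 − d/(−ln(1 − d)) | Less 7-day credit | Share excluded |
|---|---|---|---|
| 10% | 1 − 0.10/0.1054 = 5.09% | 0.06% | 5.0% |
| 20% | 1 − 0.20/0.2231 = 10.37% | 0.13% | 10.2% |
| 30% | 1 − 0.30/0.3567 = 15.89% | 0.19% | 15.7% |

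With *T* = 2 or 4 years the results are almost the same (5.0% to 15.6%, and 5.0% to 15.8%). A simpler check, with patients stopping on average halfway, gives 0.5 × *d* = 5%, 10% and 15%.

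**Step 4. Events.** Follow-up is 7034 × 3 = 21,102 patient-years. At an assumed 1 event per 100 patient-years, about 211 events are expected. If the event rate is unrelated to stopping, 10.6, 21.6 and 33.1 of them fall outside the window at 10%, 20% and 30% stopping. Over assumed rates of 0.5 to 1.5 per 100 patient-years, the range is 5.3 to 49.7 events. Events that themselves prompt stopping would add to this.

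**Step 5. Would 30 days be enough?** Replacing 7 by 30 days gives 4.8%, 9.8% and 15.1%. Nearly all the excluded time lies later, so only follow-up to trial completion addresses the point.

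**The case against.** The strongest objection is that the same phrase also refers to the whole study. Read that way, time off drug in early stoppers is covered, and the request that they attend all visits fits. This cannot be ruled out. But the alternative reading also has to be inferred, so at the least the sentence leaves early stoppers unclear.

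A second objection is that this is a condensed article. The full protocol, the analysis plan or Additional file 4 may contain a separate rule for malignancy and fracture, and the text on events of special interest describes ascertainment without a time limit. That is fair as far as missing detail goes. The point here is different: a window is stated, and it carries no exception.

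Third, a reader might infer that delayed events are lost, or that the comparison is biased. The documents support neither. Events after day 7 may be recorded and only left out of the analysis. All deaths are adjudicated and all-cause mortality is a listed outcome, so a fatal malignancy is counted at least as a death. If stopping is unrelated to the event, leaving out both the off-drug events and the off-drug time need not distort a rate comparison. Nothing in the article shows that stopping differs by arm. What stands is a risk of informative truncation, not a demonstrated bias.

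Finally, a short-window analysis answers a legitimate question about effects on drug. That also stands, which is why it should be kept.

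**Conclusion.** The concern holds in limited form. The article states one adverse event window ending 7 days after the last dose and makes no exception for malignancy or bone fracture, while the same patients stay under observation and their cardiovascular outcomes are followed to trial completion. On the natural reading, the comparison of these two event types is truncated at a time that may relate to the event or differ between arms.

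The size depends wholly on assumptions. With 10% to 30% stopping early at a constant hazard and remaining in follow-up, about 5% to 16% of patient-time is excluded. On the alternative reading, early stoppers' off-drug time within the planned treatment period would not be excluded. Cardiovascular outcomes and deaths are not affected on either reading. This does not threaten the trial's primary conclusion, but it should be settled before the safety analysis is run.

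**What to change.** State how the window works for a patient who stops study drug early, and whether malignancy and fracture are collected after day 7 in such patients. Keep the 7-day analysis for adverse events generally. For malignancy and bone fracture, add a time-to-first-event analysis in the treated set, from first dose to individual trial completion, by randomised arm, shown beside the 7-day result. Collect these events at the visits already scheduled after discontinuation.

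The cost is a few sentences of analysis wording, one extra set of tables and continued event reporting at those visits. The added analysis will include background events off drug, which may dilute a true on-drug effect. Showing both results lets the reader weigh that.
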